## Abstract

**Background:**

In 2010 a Cochrane review confirmed that folic acid (FA) supplementation prevents the first- and second-time occurrence of neural tube defects (NTDs). At present some evidence from observational studies supports the hypothesis that FA supplementation can reduce the risk of all congenital malformations (CMs) or the risk of a specific and selected group of them, namely cardiac defects and oral clefts. Furthermore, the effects on the prevention of prematurity, foetal growth retardation and pre-eclampsia are unclear.

Although the most common recommendation is to take 0.4 mg/day, the problem of the most appropriate dose of FA is still open.

The aim of this project is to assess the effect a higher dose of peri-conceptional FA supplementation on reducing the occurrence of all CMs. Other aims include the promotion of pre-conceptional counselling, comparing rates of selected CMs, miscarriage, pre-eclampsia, preterm birth, small for gestational age, abruptio placentae.

**Methods/Design:**

This project is a joint effort by research groups in Italy and the Netherlands. Women of childbearing age, who intend to become pregnant within 12 months are eligible for the studies. Women are randomly assigned to receive 4 mg of FA (treatment in study) or 0.4 mg of FA (referent treatment) daily. Information on pregnancy outcomes are derived from women-and-physician information.

We foresee to analyze the data considering all the adverse outcomes of pregnancy taken together in a global end point (e.g.: CMs, miscarriage, pre-eclampsia, preterm birth, small for gestational age). A total of about 1,000 pregnancies need to be evaluated to detect an absolute reduction of the frequency of 8%. Since the sample size needed for studying outcomes separately is large, this project also promotes an international prospective meta-analysis.

**Discussion:**

The rationale of these randomized clinical trials (RCTs) is the hypothesis that a higher intake of FA is related to a higher risk reduction of NTDs, other CMs and other adverse pregnancy outcomes. Our hope is that these trials will act as catalysers, and lead to other large RCTs studying the effects of this supplementation on CMs and other infant and maternal outcomes.

**Trial registration:**

Italian trial: ClinicalTrials.gov Identifier:
NCT01244347.

Dutch trial: Dutch Trial Register ID:
NTR3161.

## Background

### Congenital malformations and other adverse outcomes

Congenital malformations (CMs) are an important public health issue in terms of impact on the quality of life of affected children, adults and their families, and are a major cause of early spontaneous abortions, termination of pregnancy, infant morbidity, mortality and disability in all industrialized countries. Even in the less developed countries, CMs are recognized as one of the major problems in the maternal-child health field.

The European Surveillance of Congenital Anomalies (EUROCAT), a network of population-based congenital anomaly registries in Europe, currently surveys more than 1.7 million births per year, including 31% of births in the European Union. EUROCAT member registries collect data, ascertained from multiple sources, on all major structural congenital and chromosomal anomalies: the prevalence rate of all anomalies, excluding chromosomal anomalies, is 219.70 per 10000 births, and the rate of neural tube defects (NTDs: anencephalus and similar, spina bifida, encephalocele) is 9.32 per 10000 births (2007–2011). Across Europe, an estimated 4500 pregnancies are affected by NTDs each year
[1].

The economic cost of CMs is very high, including long-term psychological and socio-economic effects. In particular, the lifetime direct medical cost for patients with NTDs is significant, with the majority of cost being for inpatient care, for treatment at initial diagnosis in childhood, and for comorbidities in adult life. Caregiver time costs are also significant
[2]. The lifetime indirect cost for patients with spina bifida is even greater due to increased morbidity and premature mortality
[3].

Considering other adverse pregnancy outcomes, preterm birth is the second largest direct cause of child deaths in children younger than 5 years and preterm birth complications are estimated to be responsible for 35% of the world’s 3.1 million annual neonatal deaths. Available evidence suggests that the rate of preterm birth in high-income countries is rising
[4]. The majority of this increase is due to a rise in the rate of late preterm births (between 34 and 36 weeks gestation). Preterm birth, defined as delivery prior to 37 completed weeks, is a major challenge for maternal and perinatal care worldwide and a leading cause of neonatal morbidity and mortality
[4-6]. In 2010, an estimated 14.9 million babies (range 12.3-18.1 million) were born preterm; this is 11.1% of all live births worldwide, ranging from about 5% in several European countries to 18% in some African countries. Children born prematurely have higher rates of learning disabilities, cerebral palsy, sensory deficits and respiratory illnesses compared to children born at term. These negative health and developmental effects often extend to later life, resulting in enormous medical, educational, psychological and social costs
[6-8].

Birth weight is the endpoint of different foetal growth patterns and adverse exposures that may influence foetal growth as early as the first trimester. Human growth and development rates are highest during the first trimester of pregnancy, when essential foetal organ development is completed. Foetal developmental adaptations due to adverse conditions may affect the structure, physiology and function of various organ systems, leading to foetal growth restriction and increased risks of metabolic and cardiovascular disease in adulthood. Foetal growth restriction is widely recognized as a risk factor for neonatal mortality and morbidity
[9], as well as reduced cognitive function and the development of chronic diseases in later life
[6,10,11].

Regarding maternal adverse outcomes, pre-eclampsia is a major cause of maternal mortality (15-20% in developed countries) and morbidities (acute and long-term), perinatal deaths, preterm birth and intrauterine growth restriction
[12,13]. Despite advances in perinatal care, frequency of pre-eclampsia has not changed. Several studies have also suggested that women who develop pre-eclampsia are at increased risk of cardiovascular complications later in life
[14-16], in particular hypertension, ischaemic heart disease, stroke, venous thromboembolism, and death
[17].

Primary prevention of these adverse pregnancy outcomes in the population is a crucial policy priority, including pre-conceptional care and whole population approaches
[1,7]. Furthermore, finding simple and inexpensive ways to prevent these infant and maternal adverse outcomes is salient in any setting
[2,18,19].

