The Hungarian study conducted also shows a 60% risk reduction of the Down syndrome (OR = 0.4, 95% CI 0.2-0.7) in women who had taken 6–9 mg/day of FA before pregnancy
[51]. This association was not confirmed in other conditions
[52,53].

Unfortunately, from the observational studies it is impossible to gain a precise estimate of the reduction associated with the FA supplementation. A robust study design as is obtained in an RCT is needed to confirm these results and obtain a more precise size effect.

Furthermore, the effects of FA supplementation for the prevention of other infant and maternal outcomes are unclear.

In 2005 a large RCT of FA supplementation found no evidence of an effect of supplements on mean birth weight, placental weight or gestational age at delivery. There was a possible reduction in risk of low birth weight or antepartum haemorrhage with high-dose FA supplements, and a possible reduction in risk of pre-eclampsia with low and high dose
[54].

In the recent Cochrane meta-analysis of randomized and quasi-randomized trials, there were no significant differences between experimental and control groups on other pregnancy outcomes
[33]. Considering the supplementation with FA versus any other interventions/placebo, all five trials examined the rate of miscarriage in women with confirmed pregnancy. While the number of miscarriages increased in the group receiving supplements containing FA, the difference between groups did not reach statistical significance (RR = 1.10, 95% CI 0.97-1.26). The number of babies with low birth weight (less than 2500 g) was examined in one trial (186 babies). There was no significant evidence of a difference between treatment groups. Stillbirths were reported in four trials. There was no significant evidence of any difference between treatment groups in the pooled analysis (RR = 0.96, 95% CI 0.51-1.83). The number of women affected by multiple pregnancy (2 or more foetuses at birth) was examined in three trials. Overall there was no evidence of any significant difference between women receiving supplements with FA and those in the controls (RR = 1.32, 95% CI 0.88-1.98). No trials reported results for preterm birth (less than 37 weeks’ gestation) and pre-eclampsia, defined as gestational hypertension (blood pressure higher than 140/90 mmHg) and proteinuria (more than 300 mg of protein in a 24-hour urine sample). All of the studies included were published before 2001.

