### Dutch RCT

The primary objectives are:

• to assess the effect of peri-conceptional FA supplementation of 4 mg/day compared to the 0.4 mg/day standard dose on the prevalence of CMs;

• to assess the effect of 0.8 mg *vs* 0.2 mg FA supplementation in the second and third trimesters of pregnancy on the prevalence of preterm birth and pre-eclampsia.

The project is currently going on. Despite a specific recruitment strategy in both countries, the lack of acknowledged clinical activity defined as preconceptional counselling, together with the absence of a routine setting which women planning pregnancy naturally refer to, the study cannot maintain the planned trend of recruitment.

Nonetheless, considering the relative paucity of data and the increasing interest toward the effect of FA also on other end points of the pregnancy, the need to develop further studies focusing on health outcomes of folate supplementation, together with difficulties in subjects recruitment, the research group is still engaged in the assessment of the effect of peri-conceptional FA supplementation of 4 mg/day compared to the 0.4 mg/day standard dose in reducing the occurrence of the main adverse pregnancy outcomes. The following were grouped together: CMs, miscarriage, pre-eclampsia, preterm birth, small for gestational age, abruptio placentae.

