### Information collected and follow-up

#### Italian RCT

At the enrolment visit, all the eligible women are interviewed by the investigators using a structured form to evaluate socio-demographic and lifestyle characteristics, past and present health status, previous pregnancy outcomes, and the previous four months of food intake.

After randomization, enrolled women are interviewed by the investigators every 4 months (if not pregnant), when they contact the randomization centre to get another box of FA pills. The interview at 4-8-12 months is performed using a structured form to evaluate the pregnancy status, current health conditions, and experimental medicine intake.

Enrolled randomized women who are diagnosed as being pregnant during the study period and who take the FA until the end of the 12th completed gestational week, are invited to come back to the randomization centre to return the remaining pills and to update their status.

They will be interviewed at the expected 16, 24 and 40 weeks of gestation by a trained Health Care Provider (HCP) by phone using a structured form to evaluate the pregnancy outcome. All the pregnancy outcomes, irrespective of the information reported by the woman at the interview, will be checked in the hospital’s clinical records by a trained HCP.

The health status of live births will be evaluated by a trained HCP through an interview with the attending physician using a structured questionnaire when the child reaches the age of 1 month, 3 months and 1 year, and an interview with the parents when the child is 1 year old.

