#### Dutch RCT

Most data are gathered through questionnaires in the Netherlands. Information on all CMs of live births, stillbirths and terminations of pregnancy following prenatal diagnosis are derived from the database of EUROCAT, where virtually all CMs are registered. Data about the diagnosis and the medical history are collected in a standardized procedure of high quality.

Variables derived from medical records are: birth weight, gestational age, diseases during pregnancy (diabetes, high blood pressure), abruptio placentae, Apgar score.

In a short questionnaire, women answer questions on compliance to trial medication, the use of vitamin supplements and the use of alcohol, tobacco and drugs. These questions will be repeated each time they pick up their supplements at the pharmacy.

Follow-up: after randomization, women receive a new set of pills every 4 months at the pharmacy, until a period of 12 months has elapsed without them getting pregnant or until the end of their pregnancy (live birth, stillbirth, spontaneous abortion or termination). After the pregnancy has been completed, women and their general practitioners will receive a final questionnaire about pregnancy outcomes by mail.

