#### Dutch RCT

Women are asked to return all pills they have not used to the pharmacy every time they collect a new set of pills, in order to check compliance with FA supplementation.

All analyses will be performed according to the intention-to-treat principle. In addition, alternative per protocol analyses will be performed, excluding all participants who were not compliant with FA supplementation. For the analysis on the effect of FA supplementation on CMs, groups 1 and 2 (low dose) and 3 and 4 (high dose) will be combined, since no interaction between early FA and late FA supplementation is expected.

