### Sample size

In the original protocols, sample size was computed considering CMs as end point. However, given the increasing interest toward the effect of FA supplementation on all pregnancy outcomes on the one hand, and the difficulties encountered in subjects recruitment on the other hand, we foresee to analyze the data considering all the adverse outcomes of pregnancy taken together in a global end point (e.g.: CMs, miscarriage, pre-eclampsia, preterm birth, small for gestational age, abruptio placentae).

Since the frequency of the cumulative group of adverse pregnancy outcomes has an estimated frequency of 30% (unpublished observation), a total of about 1,000 pregnancies need to be evaluated to detect an absolute reduction of the frequency of 8% with allocation ratio 1:1, alpha error of 0.05, power of 80%.

After one year of pregnancy planning or active pregnancy search, a pregnancy rate of 80-85% is expected. Since the sample size needed to analyze outcomes separately is large, this project also promotes an international prospective meta-analysis.

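### The Dutch malformation outcome leaves out miscarried pregnancies and the Italian text does not say how they enter, so a dose difference in malformations could partly reflect differential embryo loss, in either direction

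*Protocol article*

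**What the plan says.** - **CMs as a question of their own.** Objectives, Italian RCT, makes reducing the occurrence of CMs a primary objective. Objectives, Dutch RCT, does the same for the effect of 4 mg against the 0.4 mg "standard dose on the prevalence of CMs". Outcome measures, Dutch RCT, names FA-related CMs among the primary outcomes.
- **A separate Dutch CM comparison.** Definition of treatment compliance and withdrawal, Dutch RCT, fixes the grouping: "For the analysis on the effect of FA supplementation on CMs, groups 1 and 2 (low dose) and 3 and 4 (high dose") are pooled, and the two dose groups compared.
- **Where Dutch CMs come from.** Information collected and follow-up, Dutch RCT: "Information on all CMs of live births, stillbirths and terminations of pregnancy following prenatal diagnosis are derived from the database of EUROCAT". The same section names spontaneous abortion as one way a pregnancy can end, but not as a source of CMs.
- **Italian ascertainment.** Women are interviewed at 16, 24 and 40 weeks, and every pregnancy outcome is checked in hospital records. After that, "The health status of live births will be evaluated by a trained HCP" up to one year of age. Nothing is said on how a miscarried pregnancy enters the CM comparison.
- **The link between CMs and loss.** The Background says that CMs "are a major cause of early spontaneous abortions, termination of pregnancy, infant morbidity, mortality and disability".
- **Folic acid (FA) and miscarriage.** On the trials in the cited Cochrane review, the Background reports: "While the number of miscarriages increased in the group receiving supplements containing FA, the difference between groups did not reach statistical significance". That contrast is FA against no FA, with a relative risk of 1.10 and a 95% confidence interval from 0.97 to 1.26.
- **Global end point.** Objectives and Sample size group CMs with miscarriage and other outcomes. The Italian primary outcome is this group.

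**The concern.** Women are randomised before conception, and miscarriage happens after randomisation. If malformed embryos are over-represented among miscarriages, as the Background says, then a CM count that leaves out miscarriages is taken in a group selected by an event that the dose may alter. The trial itself allows for that, because miscarriage is a component of the end point on which 4 mg is expected to do better.

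Two errors are possible. If 4 mg increased the loss of malformed embryos, CM prevalence would fall with no malformation prevented. If 4 mg helped affected embryos survive, real prevention would be masked, or 4 mg would look harmful. Pooling does not help: the prospective meta-analysis that the article promotes would shrink random error but leave this bias in place.

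**Working it through.** **The plan's own figure.** Sample size gives "alpha error of 0.05, power of 80"%, allocation 1:1, and states that "the cumulative group of adverse pregnancy outcomes has an estimated frequency of 30% (unpublished observation"), to be reduced by 8 points. With p1 = 0.30, p2 = 0.22, mean 0.26 and two-sided alpha:

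n = [1.96·√(2·0.26·0.74) + 0.8416·√(0.30·0.70 + 0.22·0.78)]² / 0.08² = 471 per arm, or 496 with continuity correction. The totals are 942 and 992, so about 1,000 reproduces. This figure concerns the global end point and is not in dispute.

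**Inputs for the illustration**
- CM prevalence p = 219.70 per 10,000 births = 0.02197 (Background; non-chromosomal anomalies). It stands in for the Dutch FA-related CMs, for which no rate is given.
- Miscarriage ratio: 1.10, upper limit 1.26, lower limit 0.97 (Background; FA versus none, borrowed for 4 mg versus 0.4 mg).
- Miscarriage risk m at the lower dose: 10%, 15%, 20%. **Assumed**; the article gives none.
- Target: an apparent 20% relative fall. The Background calls a 15-20% fall in birth defects important.

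**Formula.** Per pregnancy at the lower dose, non-miscarried pregnancies are 1 − m and CMs are (1 − m)p. Extra losses at the higher dose are E = m(RR − 1). If a share f of them would otherwise have been counted as CMs, the prevalence among the remainder is

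[(1 − m)p − fE] / [(1 − m) − E].

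Setting this to 0.8p gives f = [(1 − m)p − 0.8p(1 − m − E)] / E.

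Worked case, m = 15%, RR 1.10: E = 0.015; (1 − m)p = 0.018675; 0.8 × 0.02197 × 0.835 = 0.014676; f = 0.003999 / 0.015 = 0.27.

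| Miscarriage risk (assumed) | Extra losses per 100, RR 1.10 | f, RR 1.10 | Extra losses per 100, RR 1.26 | f, RR 1.26 |
|---|---|---|---|---|
| 10% | 1.0 | 41% | 2.6 | 17% |
| 15% | 1.5 | 27% | 3.9 | 11% |
| 20% | 2.0 | 19% | 5.2 | 9% |

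**Non-selective loss.** With f = p = 2.2%, numerator and denominator shrink alike and the CM ratio per birth is 1.00. Only selective loss biases the comparison.

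**Other direction.** At RR 0.97 and m = 15%, E = −0.0045. If 27% of the pregnancies kept were malformed, prevalence would be (0.018675 + 0.001215) / 0.8545 = 0.02328, a ratio of 1.06. CMs would appear to rise although none was caused.

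**Does a per-pregnancy denominator help?** No. In the six scenarios above, the ratio per pregnancy, 1 − fE / [(1 − m)p], is 0.79-0.78 at RR 1.10 and 0.78-0.75 at RR 1.26. The false fall of 20% becomes about 21-22% and 22-25%. With non-selective loss the ratio per pregnancy is 0.989-0.975 (RR 1.10) or 0.971-0.935 (RR 1.26), where per birth it was 1.00.

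**Would requiring a joint risk no higher with 4 mg work?** Take 500 pregnancies per arm, no dose effect on miscarriage and a true 20% CM reduction. The joint risk falls by 0.2(1 − m)p: 0.40 points at m = 10% (SE 2.0) and 0.35 points at m = 20% (SE 2.6). The observed joint risk would still be higher with 4 mg with probability Φ(−0.40/2.04) = 42% to Φ(−0.35/2.60) = 45%. Such a rule would block a true effect nearly half the time.

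**Scale.** 500 × 0.02197 is about 11 CM cases per arm. Power for a true 20% reduction is about 7%; 80% power needs about 15,760 per arm.

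**The case against.** A reader might infer that both trials count CMs only in pregnancies that escape miscarriage. The article does not support that for Italy. The live-birth follow-up comes after a hospital-record check of all pregnancy outcomes, and no sentence restricts CMs to non-miscarried pregnancies. What stands for Italy is that the handling is not stated.

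A reader might also infer that 4 mg is known to raise miscarriage. It is not. The interval 0.97-1.26 includes 1, the contrast is not 4 mg against 0.4 mg, and the Background calls the link between folate insufficiency and spontaneous abortion unclear. The concern does not need that effect to be established: the trial treats miscarriage as something the dose may change, and the bias can run either way.

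It is fair to say that the main planned analysis is protected. The global end point counts a CM pregnancy that miscarries as an event, so moving it from one component to the other changes nothing. Italy also compares miscarriage rates, and the Abstract lists this as a project aim, so an imbalance could be seen. But nothing ties it to the reading of the CM result.

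It is also fair that the article states no CM denominator and may leave such detail to a fuller document. The point rests instead on what the article does fix for the Dutch trial: the source of CMs, prevalence as the measure, and the dose grouping. Finally, with about 11 cases per arm a 20% fall is about two cases, so chance dominates within this project. That stands, but it does not carry over to the pooled analysis.

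**Conclusion.** The point holds for the separate CM comparison only. In the Dutch trial the exclusion of spontaneous abortions from the CM source is written down; in the Italian trial the handling of miscarried pregnancies is open. A dose difference in CM prevalence cannot by itself be read as prevention or as harm.

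The size is illustrative. It rests on an assumed miscarriage risk of 10-20%, a borrowed ratio of 1.10 (upper limit 1.26) and an overall CM rate used for the Dutch FA-related group. Under these, 41% to 19% of extra losses (17% to 9% at 1.26) would have to be malformed to imitate a 20% reduction. The true malformed share is not in the article. Below a ratio of 1 the bias can reverse, and with non-selective loss there is none per birth. The documents do not show that the bias will occur or that it favours 4 mg. This is an inexpensive safeguard for a stated primary objective and does not affect the global end point or its sample size.

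**What to change.** Beside the separate CM comparison in each trial:

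1. State how miscarried pregnancies are handled, in particular for Italy.
2. Report, per recognised pregnancy and by dose, miscarriage and the joint outcome of miscarriage or CM, each with a confidence interval.
3. Interpret any CM difference together with these results, and state what share of any extra miscarriages would have to be malformed to explain it.

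Do not rely on changing the denominator alone, and do not make a prevention claim depend on the joint point estimate being no higher with 4 mg; the working shows why both fail.

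Cost: one extra table and some wording. Both outcomes are already needed for the global end point, so no new data or participants are required. The drawback is that the joint outcome is dominated by miscarriage and so is imprecise for CMs. It guards the interpretation but cannot replace the CM comparison.
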